#### Visit 2 (D8)

Review of adverse events (AEs), recording of NRS scores and the various other assessment scores (BPI, ESAS, HADS, STAI-Y and MQS) 4 days after stopping treatment.

#### Visit 3 (D14, 9 days after stopping treatment) and visit 4 (D21, 16 days after stopping treatment)

The same parameters as those assessed on D8 will be assessed at these visits. These parameters will reflect the patient’s state 9 days and 16 days after stopping treatment. Patients who have returned home in the meantime will be assessed at home. In every case, the assessment will be performed by a team blinded to randomization Table 1.

**Table 1 Tab1:** Study calendar

Actions	Screening visit (D-3)	D0	D0-D4	D8	D14	End of study visit (D21)
Informed consent, demographic and clinical data	X					
Clinical examination	X	X	X	X	X	X
Randomization		X				
NRS	X	X	X	X	X	X
tDCS			X			
Recording of AEs			X	X	X	X
BPI, ESAS, HADS, STAI-Y, MQS		X		X	X	X

*NRS* Numerical Rating Scale, *AEs* adverse events, *BPI* Brief Pain Inventory, *ESAS* Edmonton Symptom Assessment System, *HADS* Hospital Anxiety and Depression scale, *STAI-Y* State-Trait Anxiety Inventory (Form Y), *MQS* Medication Quantification Scale

##### Patient follow-up

In order to maximize the number of patients evaluable for the primary analysis on the mITT population (modified intention-to-treat [43]), in the event of treatment discontinuation during the D0-D4, patients will be maintained in the trial and evaluated according to the protocol at the D14 and D21 visits. Coordination between the 2 centers is ensured by a project leader ([name]) from ELSAN, who promotes the project, in conjunction with the clinical research nurse of each of the two centers. A videoconference meeting is organized every 2 months to review the progress of the protocol in each center.

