### Benefits and risks

At the individual level, pain intensity is expected to decrease by the 2nd or 3rd tDCS session, with a more marked improvement after the 5th session. This improvement is expected to last at least 4 days (D8) and up to 16 days (D21) [15, 18]. It should be possible to markedly decrease analgesic drug treatment during this period, which should result in less drowsiness and improved activities of daily living. An improvement of sleep, tiredness and mood can also be expected. The patient may be able to return home during the week after the end of treatment with a markedly reduced workload for the patient’s caregivers.

Side effects are recorded in the electronic observation booklet after each tDCS session (D0, D1, D2, D3, D4) and during the 3 subsequent evaluations (D8, D14 and D21). Side effects [32] such as headaches or vomiting that are repeated or even worsen with each tDCS may force the patient to stop the treatment if they are prolonged or poorly tolerated. The most frequent side effect is a bad tolerance of the stimulation itself. The patient may have a sensation of electrical discharge or burning sensations at the positioning of electrodes*,* especially in the event of excessive stimulation (> 2 mA) delivered by excessively small electrodes (< 20 × 20 mm) [32]. At the most, there may be a real burn on the scalp in contact with the electrode. Initially, the proper impregnation of the sponge electrodes by the saline solution will be checked and if the phenomenon continues, the stimulation intensity will be decreaed to 1.5 mA. In the event that these adverse effects persist, the treatment will be stopped. The risk of inducing seizures is almost non-existent, but it is recommended to avoid tDCS in patients with seizures not controlled by medical treatment.

A significant collective benefit could be observed, and tDCS could markedly decrease the length of hospital stay of these patients and their analgesic drug consumption and should therefore have a significant health economics impact. In parallel, the patient’s and caregivers’ quality of life could be significantly improved. In the longer term, continuation of tDCS at home would require a new organization. The development of remote treatment techniques must also be considered [24].

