### Study objective

This study is designed to evaluate the analgesic efficacy of 5 consecutive tDCS sessions to the primary motor cortex in patients with cancer pain in the palliative care setting.

The primary endpoint is the score of the numerical rating scale (NRS), which measures pain intensity on a scale from 0 to 10 [36]. The mean of 3 NRS scores recorded during the day (morning, midday and evening) will be used. The primary endpoint for analysis will be the mean variation of the pain NRS between the baseline assessment (D0) and the D8 assessment.

The secondary objectives will be to evaluate:Immediate impact of each tDCS session on pain intensity.Response rate at the end of treatment.Residual analgesic effect.Effects of TDCS on the other main symptoms likely to impair quality of life.Analgesic consumption on D0 and D8.

Secondary endpoints will be:Pain NRS score, MQS (Medication Quantification Scale [37]), including evaluation of opioid consumption expressed in oral morphine equivalent per day on D0 and D8.Pain NRS scores, recorded before and after each session.Efficacy of treatment, defined by a ≥ 20% reduction of the mean NRS score between D0 and D8 (IMMPACT recommendation in chronic pain [38]).Mean NRS score on D14 and D21 in the 2 arms.Completion of the following questionnaires and scales on D0 and D8:. BPI (Brief Pain Inventory, short form [39]).. ESAS (Edmonton Symptom Assessment System) [40].. HADS (Hospital Anxiety and Depression Scale) [41].. STAI-Y (State-Trait Anxiety Inventory (Form Y) [42]).Analgesic consumption assessed by MQS on D0 and D8.

Analysis of repeated measurements of quantitative secondary endpoints (NRS, BPI, ESAS, HADS, STAI-Y and MQS) will be based on the mean variations of the endpoint between the baseline assessment (D0) and the D21 assessment.

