### Statistical analysis

Statistical justification of the sample size: a 2-point improvement of the numerical rating scale is considered to be clinically relevant [51], which is supported by data from the study conducted by Cheung [55] on the efficacy of ketamine in a population of patients in palliative care setting (see “Clinical Parameters”).

As this is the first protocol dedicated to the treatment of painful patients in a palliative care setting with tDCS, we did not find any evidence in the literature that could help us justify the number of needed patients for the evaluation of the other clinical parameters, apart from the NRS.

On the basis of these hypotheses:A mean NRS difference of 2 points between the active tDCS arm and the sham tDCS arm,Standard deviation of 2.8,Power of 80%.Alpha risk of 5%,

32 patients per arm would be necessary, i.e. a total of 64 patients. In order to ensure sufficient power, an additional 10% of patients will be included in the study, i.e. a total of 70 patients.

The study will therefore include 70 patients: 35 in the tDCS arm and 35 in the sham tDCS arm.

The variables measured on inclusion will be described for all patients and in each of the two arms by number and percentage for each modality for qualitative variables and by minimum, maximum, mean, standard deviation and quartiles for quantitative variables. The primary efficacy population will be a modified intention-to treat (mITT) population, comprising all randomized patients who have received at least one tDCS session (active or sham) and who were evaluated on D0 (baseline) and on D8.

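### The follow-up rule for patients who stop treatment names D14 and D21 but not D8, so it does not secure the score that the primary analysis requires

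*Protocol article*

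**What the plan says.** **Purpose and content of the rule.** Patient follow-up in the protocol article covers patients who discontinue during D0-D4. Its stated aim is "In order to maximize the number of patients evaluable for the primary analysis on the mITT population". Its content is that "patients will be maintained in the trial and evaluated according to the protocol at the D14 and D21 visits". D8 is not named.

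**Primary population.** Statistical analysis defines the mITT set as randomised patients "who have received at least one tDCS session (active or sham) and who were evaluated on D0 (baseline) and on D8". A patient who stops after one to four sessions meets the treatment condition, but enters only with a D8 evaluation.

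**Primary endpoint.** Study objective defines it as "the mean variation of the pain NRS between the baseline assessment (D0) and the D8 assessment". Analysis of the primary endpoint compares the arms on the D8 score.

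**General schedule.** Visit 2 (D8) and Table 1 list a D8 assessment and make no exception for patients who stopped treatment.

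**Assessment at home.** The section on visits 3 and 4 states: "Patients who have returned home in the meantime will be assessed at home". The Visit 2 section has no such sentence, although Benefits and risks says: "The patient may be able to return home during the week after the end of treatment".

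**The concern.** The rule for discontinuers is meant to feed the primary analysis but provides only D14 and D21 scores. Those serve the secondary question of residual effect and cannot bring a patient into the mITT set. If a site follows the one rule written for discontinuers, it may not collect D8 from them, and no later analysis plan can recover a score that was never recorded.

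Two things are at stake:

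- **Precision.** Each missing D8 score removes a patient from the primary comparison.
- **Bias.** Benefits and risks says treatment will be stopped if electrical or burning sensations persist. The Interventions section says sham delivers current only for the first 30 seconds. It is a reasonable inference, though not a statement in the document, that such stopping would be more common on active stimulation. Membership of the primary set would then depend on an event after randomisation that is related to arm.

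Early return home is a second route to a missing D8 score, because home assessment is written only for the later visits.

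**Working it through.** **1. The passages side by side.**

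| Item | Section | Visit named |
|---|---|---|
| Follow-up of patients who stop | Patient follow-up | D14, D21 |
| Entry to the mITT set | Statistical analysis | D0 and D8 |
| Primary endpoint | Study objective | D0 to D8 |
| Primary comparison | Analysis of the primary endpoint | D8 |
| General calendar | Visit 2 and Table 1 | D8, D14, D21 |

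The rule and the population it is meant to serve share no post-baseline visit.

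**2. Timing of D8.** Sessions run Monday to Friday on D0-D4, so D0 is a Monday, D4 a Friday and D8 the following Tuesday. D8 therefore lies in the week in which the document says a patient may return home, but early in that week.

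**3. The plan's own sample size.** Inputs from Statistical analysis: difference 2, SD 2.8, power 80%, alpha 5% (two-sided assumed, since the sidedness is not stated). The standardised difference is 2/2.8 = 0.714. A two-sample t-test needs 31.76, rounded up to 32 per arm and 64 in total, which matches the plan. With all 70 evaluable (35 per arm), t-test power is 83.8%. The margin above 64 is 70 − 64 = 6 patients, or 6/70 = 8.6%.

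**4. Power if patients who stop have no D8 score.** The documents give no stopping rate, so the losses below are assumptions. Power comes from the noncentral t distribution with n1 + n2 − 2 degrees of freedom and noncentrality (2/2.8) × √[n1·n2/(n1 + n2)].

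| Assumed loss, active/sham | n1 (active) | n2 (sham) | Total | Power |
|---|---|---|---|---|
| 0%/0% | 35 | 35 | 70 | 83.8% |
| 5%/0% | 33.25 | 35 | 68.25 | 82.8% |
| 10%/3% | 31.5 | 33.95 | 65.45 | 81.1% |
| 20%/5% | 28 | 33.25 | 61.25 | 78.2% |

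**5. Possible bias.** Suppose that active patients who complete gain 2 points over sham, active patients who stop gain nothing, sham patients who stop do not differ from other sham patients, and nobody who stops has a D8 score. The all-treated effect is then 2 × (1 − active stopping rate), while the D8-evaluated set still estimates 2.0.

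| Active stopping | All-treated effect | Overstatement |
|---|---|---|
| 5% | 2 × 0.95 = 1.9 | 0.1 |
| 10% | 2 × 0.90 = 1.8 | 0.2 |
| 20% | 2 × 0.80 = 1.6 | 0.4 |

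**The case against.** The strongest reply is that this is a drafting omission. Patients who stop remain in the trial and are evaluated according to the protocol, Visit 2 and Table 1 schedule D8 without exception, and the rule's stated purpose makes sense only if D8 is done. That stands in part: the document nowhere says that patients who stop skip D8. A reader might infer that every discontinuer is excluded from the primary analysis. The mITT definition does not support this, because it excludes patients without a D8 score, not patients who stopped. But the specific rule still conflicts with the general calendar at the primary time point. The Visit 2 text does not settle the matter, since it describes D8 as four days after stopping treatment, which is not true of someone who stopped early.

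Three further objections limit the size of the point:

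- A reader might expect power to fall to 74.7%. That needs 20% loss in both arms (56 evaluable). With less loss on sham, two of the three scenarios in the working stay above 64 patients and 80% power.
- The bias figures assume no benefit in any active stopper, although Benefits and risks expects pain to fall by the second or third session. That section also describes steps before stopping, and the document expects few adverse effects overall. Losing patients who responded and went home early would push the estimate the other way, so the direction is not settled.
- The home-assessment gap is modest. Return home is only a possibility, few days of that week precede D8, and nothing forbids a D8 assessment at home.

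A reader might also conclude that the primary model must be replaced, or that patients without D8 must be counted as non-responders. The contradiction requires neither; both are debatable choices, and missing-data handling commonly sits in an analysis plan that is not shown.

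**Conclusion.** The point holds in limited form. The only rule specific to patients who stop treatment omits D8, while the primary population and endpoint depend on D8, so the rule as written does not do what it says it is for. Whether patients would in fact be lost depends on whether sites follow that rule literally or the general calendar.

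Under the assumed losses, the cost is small to moderate: about 1 to 6 percentage points of power relative to 83.8%, and an overstatement of about 0.1 to 0.4 point on a 2-point effect under the no-benefit assumption. These figures show scale and do not predict what will happen.

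Separately, restoring D8 to the rule would still leave a primary set conditioned on having a D8 score. That is a real weakness fixed by the protocol itself, and a supporting analysis can address it.

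**What to change.** 1. In Patient follow-up, have the rule name the D8, D14 and D21 visits, and reconcile it with Visit 2, Table 1 and the mITT definition.
2. In the visit sections, state that patients already at home are assessed there on D8 as well as on D14 and D21.
3. As a supporting analysis, report the D8 contrast in all randomised patients with at least one session, using a mixed model on the NRS scores already collected (D0-D4, D8, D14, D21). The planned primary analysis can stay.

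The first two changes are wording only, since D8 is already a scheduled visit; the second may mean some extra home visits. The third needs no new data and does not change the sample size. Its small downside is a missing-at-random assumption, which should be stated with the result.

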#### Analysis of the primary endpoint

Analysis of the primary endpoint, the pain NRS, will be performed on the mITT population.

The mean NRS score on D8 will be compared between the active tDCS arm and the sham tDCS arm using a mixed linear model in order to take stratification factors into account.

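### The follow-up rule for patients who stop tDCS early names D14 and D21 but not D8, the visit on which the primary endpoint and mITT membership depend, and so conflicts with the general schedule

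*Protocol article*

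**What the plan says.** All references are to the protocol article.

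- **Rule for early stoppers (Patient follow-up).** The purpose comes first: "In order to maximize the number of patients evaluable for the primary analysis on the mITT population". The rule for anyone who discontinues during D0-D4 follows: "patients will be maintained in the trial and evaluated according to the protocol at the D14 and D21 visits". This is the only rule in the article specific to these patients.
- **Primary endpoint (Study objective).** It is the "mean variation of the pain NRS between the baseline assessment (D0) and the D8 assessment".
- **Primary population (Statistical analysis).** The mITT population contains randomised patients "who have received at least one tDCS session (active or sham) and who were evaluated on D0 (baseline) and on D8".
- **Primary analysis (Analysis of the primary endpoint).** On that population, "The mean NRS score on D8 will be compared between the active tDCS arm and the sham tDCS arm using a mixed linear model".
- **General schedule.** Visit 2 (D8) provides for "Review of adverse events (AEs), recording of NRS scores and the various other assessment scores". Table 1 marks the NRS, adverse events and all questionnaires at D8. The Fig. 1 legend and Benefits and risks both list D8, D14 and D21 as the follow-up assessments. None of these makes an exception for patients who stopped early.
- **A reason for stopping (Benefits and risks).** On poor tolerance of the stimulation: "In the event that these adverse effects persist, the treatment will be stopped".

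**The concern.** The rule states a purpose and then lists two visits that cannot achieve it. D14 and D21 scores do not make anyone evaluable for a D8 analysis. Only a D8 score does, and D8 is the one post-treatment visit that the rule leaves out.

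A site that treats the list as the complete set of visits for an early stopper would omit D8. The patient would then fail the mITT condition because of something that happened after randomisation. One documented reason for stopping is poor tolerance of the stimulation, so the patients lost need not resemble those kept, nor be lost equally from the two arms. The comparison would then no longer be fully protected by randomisation. The same patients would also lack the D0-to-D8 secondary endpoints (response, MQS, BPI, ESAS, HADS, STAI-Y). A missed D8 score, which is the mean of three ratings on one day, cannot be recovered afterwards.

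**Working it through.** **1. The passages side by side**

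| Question | Place in the article | Answer |
|---|---|---|
| Why keep early stoppers in the trial? | Patient follow-up | For the primary mITT analysis |
| Which visits does the rule name for them? | Patient follow-up | D14, D21 |
| When is the primary endpoint measured? | Study objective; Analysis of the primary endpoint | D8 |
| What admits a patient to the mITT population? | Statistical analysis | At least one session, evaluated on D0 and on D8 |
| Does the general schedule include D8? | Visit 2 (D8); Table 1; Fig. 1 legend; Benefits and risks | Yes, without exception |

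Rows 1 and 2 fit rows 3 and 4 only if D8 is also done. Row 5 says that it is; row 2 does not. That is the conflict.

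**2. The plan's own sample size**

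Inputs from Statistical analysis: difference 2, SD 2.8, power 80%, alpha 5% (sidedness is not stated; two-sided is assumed here and reproduces the figure).

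- Standardised difference: 2 / 2.8 = 0.714.
- Two-sample t-test: 31.76 per arm, rounded up to 32, or 64 in total. This matches the plan.
- Adding 10%: 64 × 1.10 = 70.4, given as 70. This also matches.

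The sample-size figures are not in error on this point.

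**3. Power if early stoppers lack a D8 score (illustration)**

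The article gives no stopping rate. Assume an equal proportion d lost in each arm, with the effect still 2 points. Evaluable patients per arm = 35 × (1 − d); power is from the two-sided t-test.

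| Assumed loss d | Per arm | Power |
|---|---|---|
| 0% | 35 | 83.8% |
| 5% | 33.25 | 81.8% |
| 8.6% (3 per arm) | 32 | 80.3% |
| 10% | 31.5 | 79.7% |
| 15% | 29.75 | 77.3% |
| 20% | 28 | 74.7% |

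The 10% allowance is used up at about 3 patients per arm.

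**4. Whether power is the right argument**

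Take a different assumption: a proportion p of the active arm stops early and gets no benefit, and nobody is lost from sham. With everyone analysed, the effect is 2 × (1 − p) at 35 per arm. With the stoppers excluded, it is 2.0 with 35 × (1 − p) active and 35 sham.

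| p | Effect, all analysed | Power, all analysed | Power, stoppers excluded (effect 2.0) |
|---|---|---|---|
| 5% | 1.9 | 79.9% | 82.8% |
| 10% | 1.8 | 75.5% | 81.7% |
| 15% | 1.7 | 70.7% | 80.5% |

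Under this assumption, keeping the stoppers lowers power; what it protects is the comparison as randomised. The tables in steps 3 and 4 rest on different assumptions and must not be added together. The case for the change is the contradiction and the possible bias, not lost power.

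**The case against.** The best reply is that nothing in the rule cancels D8. It keeps these patients in the trial and has them assessed as the protocol provides, and the protocol provides for D8 in four places without exception. Omitting D8 would also defeat the purpose that the rule itself states. A careful site working from Table 1 would do the visit. All of this stands: the omission is most likely a slip.

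Three stronger readings are tempting, and the documents do not support them.

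- **That early stoppers are definitely removed from the primary analysis.** This requires reading the two named visits as exclusive. The text does not say so, and the general schedule points the other way. Removal is a risk of literal application, not a certainty.
- **That their D14 and D21 data belong to no analysis population.** The mITT population is declared as the primary efficacy population, and the per-protocol set is a subset of it. Analysis of secondary endpoints names no population for the D14 and D21 analyses, so exclusion there is not shown. That detail may properly sit in a statistical analysis plan.
- **That the active arm will lose more patients and the effect will be overstated by a known amount.** Twenty minutes of active current against 30 seconds in the sham makes unequal stopping conceivable. But the Interventions section says that sensations are limited to the first 30 seconds, Benefits and risks describes steps to be taken before stopping for poor tolerance, and few adverse effects are expected. No stopping rate is given, overall or by arm.

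What remains is that the only rule written for these patients omits the primary visit, and that a site could follow it as written.

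**Conclusion.** The point holds as an internal conflict that should be corrected. The rule for early stoppers names D14 and D21; the primary endpoint and mITT membership depend on D8; the general schedule includes D8 for everyone. The inconsistency can be seen in the text and needs no assumption.

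The consequence is conditional. If sites apply the rule literally, early stoppers drop out of the primary population after randomisation, possibly for reasons of tolerance, and the D8 comparison could be biased. Neither the size nor the direction of that bias can be computed from the article. The power figures (about 80% at 10% loss and 75% at 20%, against 84% with all 70) assume equal loss in both arms, an unchanged 2-point effect and a two-sided test, and they are illustrative only. No figure in the plan needs to change.

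**What to change.** Amend Patient follow-up to say that patients who discontinue treatment during D0-D4 remain in the trial and are evaluated at D8, D14 and D21, on the calendar counted from D0 as in Table 1, and that their D8 score enters the primary mITT analysis in the arm to which they were allocated.

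The cost is one line in the protocol and a reminder to the two centres. The D8 visit and its assessments are already scheduled, so no new visit type is needed. The change concerns assessment and analysis only and leaves the treatment and stopping rules as they are. It should be made before further patients reach D8, since a missed score cannot be collected later.
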